
### Implementation outcomes, measures, and analyses

In this sub-section, implementation evaluation will be described, including implementation outcomes, adaptation and implementation of the intervention.

#### Implementation outcomes and measures

Implementation outcomes that will be assessed in this study are defined in Tables 2 and 3 and include adoption, acceptability, feasibility, and fidelity.

**Table 2 Tab2:** Study Implementation Evaluation Summary

Question/Focus	Definition/Data Source	Method of Analysis
Implementation outcomes a) Adoption (uptake) b) Acceptability c) Feasibility d) Fidelity	a) Engagement rate b) Post-intervention interviews with clients, caregivers, intervention providers and program managers c) Recruitment rate d) Fidelity checklist	a) Proportion of intervention participants who receive at least one home/telephone/videoconference visit and attend at least one group wellness session Dose of the intervention defined as number of home/telephone/videoconference visits and number of group wellness sessions b) Qualitative content analysis c) Proportion of eligible individuals who enrolled in the study
Implementation and adaptation of intervention	Research team meeting notes Research coordinator notes Interviews with intervention team and program managers Notes from Community Advisory Board meetings and focus groups	The Consolidated Framework for Implementation Research (CFIR) [91] and Normalization Process Theory [92] will be used to guide the development of interview and focus group guides and CFIR will serve as a framework for data coding and analysis. Directed content analysis will be conducted [93].
Sustainability and scalability	Research team meeting notes Research coordinator notes Interviews with intervention team and program managers Notes from Community Advisory Board meetings and focus groups Notes from Steering Committee	Content analysis [93] will be used to identify themes related to the sustainability and scalability of the intervention [94, 95]

**Table 3 Tab3:** ACHRU-CPP Intervention Fidelity Guide

Program Components	Data Source(s)
*Staffing and Supervision*	
• Intervention team receives training targeted to learning need	Record of attendance Learning needs assessment
• Monthly outreach meetings between the intervention team and investigators	Meeting notes
*Home visits (in-home, telephone or videoconference)*	
• Up to 3 home/telephone/videoconference visits conducted by the Registered Nurse/Registered Dietitian/Nutritionist	Home visit record
• Screening for diabetes-related complications and comorbidities • Review of medications	Home visit record Standardized clinical assessment tools Medication record Alerts (e.g., medication, diabetes complications)
• Assessment of self-management of diabetes and other chronic conditions and identification of client’s needs and goals • Assessment of caregiver needs (if applicable) • Motivational interviewing to foster behavioural change and encourage self-care	Home visit record My action plan Client-centred care plan Caregiver Strain Index
*Monthly Group Wellness Sessions*	
• Attend up to 6 monthly sessions led by the intervention team • Individual consultations with community program coordinator	Group wellness session record Record of individual consultations with community program coordinator
• Provision of transportation (if needed)	Group wellness session record
*Care Coordination and System Navigation*	
• Registered Nurse helps clients access supports and services in the community as needed	Client-centred care plan
*Monthly Case Conferences*	
• Intervention team attends monthly case conferences	Case conference meeting record
• Intervention team develops and re-evaluates a coordinated care plan for each participant	Client-centred care plan

Interview and focus group data collection guides for clients, caregivers, intervention team members and public and community research partners (available in Additional Files 1, 2, 3 and 4) were developed to assess perceptions of the acceptability, feasibility, implementation, perceived impact, and scalability of the intervention. Constructs from the Normalization Process Theory (NPT) [92] and the Consolidated Framework for Implementation Research (CFIR) [91] were used to develop questions in the interview and focus group guides. Focus groups and interviews with the intervention team and their managers will be held approximately 3 months after the start of the intervention and at the conclusion of the intervention. All members of the intervention team and their managers will be invited to attend the focus groups. In interviews and focus groups, public and community partners will be asked questions about implementation of the intervention based on the CFIR [91] framework as well as questions about their experiences with patient engagement in the study.

#### Adaptation and implementation of the intervention

We will use the framework developed by Stirman and colleagues [96] for reporting adaptations and modifications to evidence-based interventions to track the adaptations made to the intervention over the study period. These will include a description of when and how the adaptations occurred, whether they were planned or unplanned, how fidelity of the intervention was maintained while adapting the intervention, and reasons for and impact of adaptations.

Several data sources will be used to assess implementation outcomes and evaluate how the intervention was implemented and adapted in each of the study sites. These will include: (a) notes of meetings between the intervention team and researchers over the course of the study; (b) transcripts of focus groups and interviews with the intervention team and managers; (c) notes made by the RC and research team members over the course of the study; and (d) notes from the CAB meetings and focus groups with CAB members.

#### Analysis: implementation evaluation

##### Quantitative Data

Descriptive statistics will be used to summarize data related to the adoption of the intervention (i.e., engagement rate, dose of intervention) and the level of fidelity to treatment for each core component of the intervention at 6 months. A fidelity guide (See Table 3) will be used to assess the degree to which the following intervention components are addressed: (a) staffing and supervision (e.g., interventionists receive training and meet monthly with the investigators); (b) home/telephone visits (e.g., up to 3 visits conducted, review of medications, assessment of self-management of diabetes); (c) monthly group wellness sessions (e.g., participants attend up to 6 sessions); (d) care coordination and communication with primary care (e.g., RN helps clients access community supports and services); and (e) monthly case conferences (e.g., interventionists attend monthly case conferences; development of care plan for each client). Frequency and percentages will be used for categorical outcomes and means and standard deviations will be used for continuous outcomes.

##### Qualitative data

All interview and focus group data will be transcribed verbatim, cleaned, and entered into a qualitative data software program (NVivo Version 12, QSR). Directed content analysis [93] will be used to identify codes and themes in the data. The CFIR [91] will be used as a guiding framework for coding the interview data related to implementation. Interviews and focus group data related to the public and community partner engagement strategy will be analyzed inductively to explore both implementation and impacts of engagement (e.g., personal, professional, and research impacts). Two research team members will meet to develop the initial coding structure based on the theoretical frameworks used to develop interview questions (e.g., NPT, CFIR) and review early transcripts and notes from each data source, and the remaining data will be coded using the revised coding framework. All researchers involved in qualitative data analysis will meet regularly to review the coding framework, interim codes and themes, and reach consensus on the final themes.

### Scalability outcomes, measures, and analysis

#### Rationale for designing the trial with scale-up in mind

Planning for scale-up should be part of study design and implementation for many reasons [34]. First, scaling-up often requires changes to areas such as policies, protocols and systems. These changes take time to implement; therefore, planning for needed changes should start as early as possible. Second, supports available in trials are usually more than what can be sustained when interventions are taken to scale, so mechanisms to sustain the intervention need to be developed during study implementation to enable scale-up. Third, there are significant pressures to scale-up interventions like the ACHRU-CPP where existing evidence is promising, particularly given the high number of interventions scaled-up in the absence of any evidence [97]. In a systematic review on scaling-up primary care programs, authors noted vast inconsistencies in scaling-up reports, with none reporting information on assessing scalability [33]. Therefore, experts have stressed the need to use an incremental approach to scale-up with ongoing monitoring of implementation and effectiveness to build a scale-up evidence base [34].

We will conduct a scalability assessment as part of this study, to determine the potential for scale-up of the ACHRU-CPP intervention. The scalability assessment aims to help build the evidence base for the intervention and provide policy-makers and providers with useful tools and resources to serve as the foundation for scale-up planning after the trial ends.

#### Scalability outcomes and measures

A scalability assessment is the first step in scaling up interventions at the population level [94]. The Intervention Scalability Assessment Tool (ISAT) [95] will be used to guide the scalability assessment. Pilot testing of the ISAT has indicated that this tool is perceived as useful to assess scalability and can be applied to a variety of real-world health interventions [98]. ISAT addresses the following outcomes (called domains): Part A describes the problem, intervention, political context, effectiveness and costs/benefits; Part B considers intervention fidelity, adaptations, reach, acceptability, implementation infrastructure (e.g., provider expertise required to deliver the intervention), and sustainability; and Part C is a summative assessment based on questions from Parts A and B that supports a final recommendation on the suitability of the intervention for scale-up [95]. A number of these outcomes (domains) and related measures were discussed above (e.g., intervention, effectiveness, costs, fidelity, adaptations, acceptability) and are summarized using a range of quantitative and qualitative data.

Data sources will include the following: (a) results of the original feasibility study [30], results of the previous trial [31, 32]; (b) results of the effectiveness of the proposed trial; (c) post-intervention interviews with clients and caregivers at each site; (d) focus groups and interviews with intervention team providers and program managers from each site, and (e) notes from meetings of the intervention team, CABs and the Steering Committee.

#### Analysis: scalability assessment

The ISAT [95] consists of items to be considered for each of the domains covered in Parts A and B, and at the end of each domain there are several questions rated on a scale from 0 to 3 representing the readiness assessment of that domain. Part C combines the results of the assessments for each domain and displays the results in the form of a spider web plot, which summarizes the strengths and weaknesses of the intervention and enables comparison across the domains [95]. We will use the ISAT to create spider web plots summarizing the readiness for scale-up at each site.

The scalability assessment, as with scale-up itself, requires collaboration and the collective effort of multiple stakeholders. Therefore, a team approach will be used to complete the ISAT, with the team consisting of the researchers, intervention team, managers, and members of the CABs and Steering Committee. Difficult issues will need to be considered during this process, such as when sufficient evidence exists to determine the suitability for scale-up, how the intervention can be adapted to diverse settings while maintaining fidelity, how the intervention can become sustainable over the medium- and long-term, where scale-up will begin, and important strategic/political/environmental contextual factors that influence scale-up.

### Other outcomes, measures and analyses

#### Intervention team outcomes and measure

To better understand the impact of the intervention on interprofessional team function, the Partnership Self-Assessment Tool (PSAT) [77] will be administered to the intervention team (i.e., RN, RD/Nutritionist, PC, and their managers) near the start and end of the intervention at each site. The PSAT includes items on synergy, leadership, efficiency, administration and management, resources, decision making, benefits and drawbacks of partnership and satisfaction with the partnership.

#### Public and community partner outcome and measures

The public and community partner engagement strategy will be evaluated using surveys completed by members of the CABs and patient/caregiver research partners: (a) the Quality Involvement Measure [78]; (b) the Patient-Centred Outcomes Research Institute’s Ways of Engaging-Engagement Activity Tool (WE-ENACT) Patient/Stakeholder 2.0 self-report tool [79]; and (c) selected items from the Patient-Centred Outcomes Research Institute’s Engagement Activity Inventory NET-ENACT tool [80]. CAB members will also be invited to participate in focus groups at two time points (e.g., near the start and the end of implementation in each site) to explore perspectives on study engagement strategies. Similarly, co-investigator patient partners will be invited to participate in individual interviews for their views on the engagement strategy.

#### Analysis: other outcomes evaluation

We anticipate that small sample sizes will limit the ability to conduct inferential statistical analyses of the data from the PSAT and surveys completed by the public and community partners. Therefore, descriptive statistical analyses will be used to summarize the key responses, patterns and trends evident in these survey data.

### Ethics

The study is being conducted in accordance with the Tri-Council Policy Statement, Ethical Conduct for Research Involving Humans [99]. Institutional ethics approval was obtained from the following: the Hamilton Integrated Research Ethics Board (#5101); the Scarborough Health Network Research Ethics Board (#NEP-18-014); the Unity Health Toronto Research Ethics Board (#18-336); University of Prince Edward Island Research Ethics Board (#6008019); Prince Edward Island Research Ethics Board; and Centre intégré universitaire de santé et de services sociaux (CIUSSS) de la Capitale-Nationale (MP-13-2019-1670). Ethics approval will be renewed on an annual basis as required for the study duration. Informed consent will be obtained from participants (older adults, caregivers, providers, managers, public and community partners) by the RA before study enrolment.

### Modifications triggered by COVID-19 pandemic

Below we discuss the details of all pandemic-related impacts and changes made to the protocol to address/mitigate them.

#### Overview of pandemic impact, importance and key decisions

The trial was underway at all sites at the time that the COVID-19 pandemic hit Canada (March 2020). As noted in the CONSERVE guidelines, the impact of the pandemic on studies already underway “is an exemplar” of extenuating circumstances that are unavoidable and beyond the control of the investigators, funding agencies, and trial sites [58]. In our study, the pandemic resulted in a range of impacts at the sites, including delays in the implementation of the intervention, discontinuation of the intervention, and shifting from in-person to virtual delivery of the intervention and data collection methods. These impacts in turn triggered important modifications to the study protocol that had implications for the study feasibility, intervention implementation, intervention effectiveness, and analytical methods in the trial. The research team planned, reviewed and achieved consensus on the mitigation strategies proposed to address the pandemic impacts.

The pandemic resulted in stopping the study at all sites on March 16, 2020. The next steps at each site were dependent on the stage of the study at the site, with the result being the offering of different doses and/or delivery formats for the intervention to participants within and across sites. We moved to virtual approaches to deliver the intervention and to collect data at all sites, which required obtaining ethics approvals at the sites. One site had the intervention team re-deployed to deal with COVID-19 issues and the intervention could not be restarted. The details of these and other impacts and the mitigation strategy to address them are outlined below for the SPIRIT checklist items that were affected.

#### Trial Registration, protocol version, amendments, research ethics approvals

The shift to virtual delivery of the intervention by videoconference and virtual data collection by telephone resulted in updates to the trial registration, various amendments to the study protocol, and re-submissions to the institutional ethics boards at each site to obtain approval for these changes to the methods.

#### Funding

Delays in implementing the intervention at several sites resulted in extending the study duration past the original deadline outlined in the funding agreements. Fortunately, funding agencies provided a one-year extension to assist with delays resulting from the pandemic.

#### Roles and responsibilities

The roles of the intervention team, RCs and RAs will not change, in that they will still be responsible for delivering the intervention, monitoring trial performance, and collecting data. However, the shift to virtual delivery and data collection requires additional access to secure virtual technology and the ability to use it effectively to deliver care and obtain data. Also, RCs and intervention team members will take on additional responsibilities related to training participants in the use of technology to support the virtual receipt of the intervention. Overall, the intervention team, RCs and RAs are technologically-capable, and investigators will support them as necessary to ensure that any technological challenges will be addressed.

#### Study setting

The trial had to be completely stopped at one of the Quebec sites due to the re-deployment of members of the intervention team to deal with COVID-19 issues. The research team from Prince Edward Island has agreed to recruit an additional 44 participants and provide the intervention virtually by videoconference or by telephone, based on the participant’s preferences, using the same RA, RC and intervention team. Although this reduces the diversity of our sample due to a smaller representation from the province of Quebec, it allows us to preserve the overall sample size of the study.

#### Intervention

The virtual delivery of the home/telephone visits and the group wellness sessions has been proposed to allow the intervention to proceed where the trial was either already underway or about to begin (see *Overview of Pandemic Impact, Importance, and Key Decisions*). The shift to this virtual environment may present challenges to participants, in that they may not be comfortable with videoconferencing technology or have access to it or the Internet/Wi-Fi. For the intervention team, some clinical assessment tools need to be eliminated as they cannot be administered virtually (e.g., frailty assessment, Timed Up and Go (mobility) tests, home environment assessment), which may impact the development of care plans. Further, the monthly team case conferences, originally proposed as in-person team meetings, need to shift to virtual meetings, which may impact team collaboration.

A range of mitigation strategies have been proposed to address these impacts. For the duration of the intervention, tablets and/or Internet/Wi-Fi access will be provided to all participants that require these to enable their virtual participation in the intervention. RCs will train all participants on the use of the tablets and Internet/Wi-Fi as needed. Most clinical assessment tools have remained in place and can be administered virtually, thus the elimination of a select few is not expected to significantly impact the development of a care plan. Maintaining regular case conference schedules as well as increased comfort with online communications are expected to continue to facilitate team collaboration.

#### Participant timeline

Delays in starting and continuing the intervention at some sites resulted in extending the duration of the study past the planned study end dates. Even with the one-year extensions granted by the funding agencies, the planned 12-month follow-up assessment exceeded the end dates of the study at some sites. The mitigation strategy proposed to address this issue was to eliminate the 12-month follow up assessment.

#### Sample size

Sample size will be maintained despite the loss of one of the Quebec sites due to the Prince Edward Island research team offering to recruit an additional 44 participants.

#### Recruitment

Delays in starting the intervention have resulted in recruiting participants at different points in time at the sites, some prior to the pandemic and others during the pandemic. If participants are more recently enrolled at the sites, it is possible that the types of patients or the severity of their diabetes or other chronic conditions may differ from those recruited prior to the pandemic. This has been a concern for acute care sites during the pandemic, but likely less to be an issue in the community-based settings where we are recruiting. Number of chronic conditions is a variable included in our subgroup analyses, which may help in exploring differential effects in participant health status.

#### Data collection methods

All data collection shifted from in-person to virtual methods (phone or video) once the pandemic hit. The collection of data from trial participants by the RAs will be done strictly by telephone. Interview/focus group data from site managers, intervention teams, and CAB members will be done by telephone or videoconference. While this shift triggered a series of changes to the consent forms, no changes were made to the actual data that will be collected.

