### Data collection

#### Participant flow, assessments, and timeline

RAs will conduct two assessments (home or telephone interview) with each study participant, one at baseline (T1) and the other at the end of the 6-month intervention period, 6 months after baseline (T2). Baseline data will be collected on socio-demographic, clinical, and primary and secondary outcome variables. Each assessment will take approximately 1.5 hours to complete. The Research Coordinator (RC) will meet regularly with the RAs to address questions and concerns and ensure consistency of approach across the sites. The RC will check the data throughout the data collection process to ensure minimal errors and missing data. Participant flow through the study will be illustrated using a flow diagram which conforms to the CONSORT guidelines [61] for reporting pragmatic trials (See Fig. 1).

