#### Analysis: effectiveness evaluation (older adult and caregiver participants)

The baseline demographic and clinical characteristics of participants who completed both the baseline and 6-month assessments will be compared. Descriptive statistical analysis will be used to summarize outcome variables at baseline and 6 months. For continuous variables, means and standard deviations will be calculated, and for categorical variables, frequencies and proportions will be assessed. Analysis of covariance (ANCOVA) will be used to test the differences in outcome variables between the intervention and control group at 6 months. Separate ANCOVA models will be run for each primary and secondary outcome, with the 6-month change in the outcome as the dependent variable, group (intervention, control) as the independent variable, and the baseline value of the outcome as the covariate.

Statistical tests will use a 0.05 two-tailed level of significance and 95% confidence levels. An intention-to-treat (ITT) approach unadjusted for baseline characteristics will represent the primary analysis, using multiple imputation for missing data. Costs will be applied to the health and social service use reported by clients and caregivers. Group differences in the 6-month change in service use costs will be examined using parametric or non-parametric methods, depending on the distributional properties of the cost data [83].

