#### Statistical methods

As noted in *Overview of Pandemic Impact, Importance, and Key Decisions*, decisions on how to proceed with the trial were dependent on the stage of the trial at each site, resulting in variation across intervention participants in terms of the number of home/virtual visits and group wellness sessions that can be offered and the extent to which the intervention components can be delivered virtually versus in person. At all sites, intervention participants will be offered a minimum of one home/virtual visit and one group wellness session. Some clinical assessments were eliminated in the shift to a virtual format, which could result in less information being available to inform the development of a care plan for participants. RAs had to shift to collecting participant data by telephone instead of in person, which could affect the quality of the data collected.

The collective impact of these COVID-related changes on the effectiveness of the intervention is uncertain. Previous trials have not shown a significant dose-response for the intervention, suggesting that a minimum dose of one home/telephone visit and group session may be sufficient [31, 32]. There is some evidence from comparative effectiveness research on similar interventions that outcomes may not change with virtual delivery [100], and other studies cite a range of potential benefits of virtual approaches to diabetes care during the pandemic [101].

We plan to carefully track the type of intervention participants receive and to compare effectiveness and implementation issues for those receiving in-person versus virtual approaches to care. In addition to the pre-planned subgroup analyses noted above, we will conduct a subgroup analysis comparing the effectiveness of the intervention across groups of participants classified according to meaningful differences in exposure to the virtual platform. This subgroup analysis, as with all subgroup analyses, will be regarded as exploratory and offered as relevant background subject to cautious interpretation [85, 87].

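### Client interviews went telephone-only after 16 March 2020 and recruitment straddles that date, yet no stated model has a period term; the cost is a small loss of precision

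*Protocol article*

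**What the plan says.** All places are in the protocol article.

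- **Interruption** (Overview of pandemic impact, importance and key decisions): "The pandemic resulted in stopping the study at all sites on March 16, 2020". The opening of Methods says the trial had begun in 2019.
- **Interview mode afterwards** (Data collection methods, within the COVID-19 modifications): "All data collection shifted from in-person to virtual methods (phone or video) once the pandemic hit", and for trial participants "The collection of data from trial participants by the RAs will be done strictly by telephone".
- **Interview mode as designed** (Participant flow, assessments, and timeline): "RAs will conduct two assessments (home or telephone interview) with each study participant". Telephone was therefore already permitted. The Caregivers section has every caregiver interview by telephone from the start.
- **Conceded effect on data** (Statistical methods, within the COVID-19 modifications): "RAs had to shift to collecting participant data by telephone instead of in person, which could affect the quality of the data collected".
- **Case mix by period** (Recruitment, within the COVID-19 modifications): some participants were recruited before the pandemic and others during it, and the two groups may differ. The response offered is: "Number of chronic conditions is a variable included in our subgroup analyses, which may help in exploring differential effects in participant health status".
- **Primary model** (Analysis: effectiveness evaluation): the 6-month change is regressed on "group (intervention, control) as the independent variable, and the baseline value of the outcome as the covariate". The same section adds: "An intention-to-treat (ITT) approach unadjusted for baseline characteristics will represent the primary analysis, using multiple imputation for missing data".
- **Sensitivity analyses** (same section): complete case; adjustment for significant baseline imbalance; site as covariate; distributional checks with non-parametric methods; exclusion of intervention participants who received nothing. The COVID-19 modifications add an exploratory subgroup by exposure to the virtual platform.

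**The concern.** The stop date splits clients into up to three groups: both interviews before it, T1 before and T2 after, and both after. In the middle group the 6-month change also carries whatever the change of interview mode and the pandemic did to MCS. In the last group both interviews were taken under the later conditions. The article recognises the possible differences but names no analysis that accounts for them.

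The stated analyses do not fill the gap:

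- A count of chronic conditions records neither when nor how someone was interviewed.
- Exposure to the virtual platform describes how the intervention was delivered. The article does not say how control participants would be classified.
- Site is only a partial proxy. Exposure varied within as well as across sites, and the Prince Edward Island team recruits 44 further participants during the pandemic with the same staff.
- The imbalance adjustment runs only if the arms differ significantly, and randomisation should balance period.

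At stake are some precision in the primary comparison, the soundness of the imputation if loss was uneven, and the readability of the descriptive T1 to T2 changes.

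**Working it through.** **Inputs from the article.** Mean difference 3.68, SD 9.68, 80% power, two-sided 0.05, 20% attrition, total 264, 1:1 permuted blocks within site.

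**Inputs assumed, because the article gives none.** Baseline to 6-month correlation 0.5; cohort shares 25% (before/before), 35% (before/after), 40% (after/after); a shift m of 2 to 6 MCS points, equal in both arms; block size 4 in the site-based simulation.

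**1. The plan's own figure.** An exact two-sample t-test needs 110 per arm, 220 in total, and 220 × 1.20 = 264. With 20% lost, 264 × 0.80 / 2 = 105.6 per arm remain.

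**2. Baseline precision.** Residual variance after baseline adjustment is 9.68² × (1 − 0.5²) = 70.28. SE = √(70.28 × 2 / 105.6) = 1.154.

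**3. Loss of precision.** An unmodelled shift adds the between-cohort variance of the baseline-adjusted outcome, so the SE is multiplied by √(1 + added variance / 70.28).

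- *Pattern A*, shift in the interrupted cohort only: added variance 0.35 × 0.65 × m² = 0.2275 m².
- *Pattern B*, telephone shifts T2 in both later cohorts and T1 in the last one: baseline-adjusted shifts are 0, m and 0.5m. Added variance is (0.35 + 0.40 × 0.25 − 0.55²) m² = 0.1475 m².

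| m | A: added variance | A: SE increase | B: added variance | B: SE increase |
|---|---|---|---|---|
| 2 | 0.91 | 0.6% | 0.59 | 0.4% |
| 4 | 3.64 | 2.6% | 2.36 | 1.7% |
| 6 | 8.19 | 5.7% | 5.31 | 3.7% |

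A simulation of the ANCOVA with n = 264 and 20% loss (4,000 runs per setting) compared models without and with the cohort terms, so it nets off the two degrees of freedom. The increases were 0.5%, 2.5% and 5.5% for A, and 0.3%, 1.6% and 3.5% for B. With no shift, the term cost 0.1 to 0.2%.

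**4. Power, by the two-sample formula at 105.6 per arm, half the participants shifted.** SD becomes √(9.68² + 0.25 m²). Power is 0.789 with no shift, 0.785 at 2 points, 0.779 at 3 and 0.763 at 5 (SD 10.00).

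**5. Bias when the shift and the loss are equal in both arms.** A second simulation used six sites of 44, permuted blocks and 3,000 runs, with shifts of 0, 2 and 5 points. The mean estimate (truth 3.68) was 3.70, 3.67 and 3.69 both without and with the term. Type I error was 0.048, 0.043 and 0.044 without it, and 0.049, 0.043 and 0.051 with it.

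**6. Bias when loss also differs by arm.** Assume 35% loss in one arm and 20% in the other, in the interrupted cohort only, and 20% elsewhere. In the arm with more loss the interrupted share of completers is 0.35 × 0.65 / (0.35 × 0.65 + 0.65 × 0.80) = 0.2275 / 0.7475 = 0.304, against 0.350 in the other arm. The last cohort's share is 0.40 × 0.80 / 0.7475 = 0.428, against 0.400.

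- Pattern A: bias = (0.350 − 0.304) m = 0.046 m, which is 0.09, 0.18 and 0.27 points for m = 2, 4, 6.
- Pattern B: bias = [0.55 − (0.304 + 0.5 × 0.428)] m = 0.032 m, which is 0.06, 0.13 and 0.19 points.

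This is a completer calculation. Imputation from arm and baseline value alone would be expected to give much the same. With the cohort term the simulated bias was close to zero. Its sign depends on which arm loses more and on the direction of the shift.

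**The case against.** The case against is substantial, and most of it stands.

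- **The randomised comparison is protected.** With 1:1 permuted blocks within site, period is close to balanced between arms. A reader might infer that pooling interview conditions biases the treatment effect. For a shift common to both arms it does not (step 5).
- **Chronic-condition count is not the only response to the pandemic.** A reader might take it so, but the article also plans a comparison of in-person with virtual care, a virtual-exposure subgroup, a site-adjusted analysis and an exclusion analysis prompted partly by COVID-19. The Recruitment text says only that the count may help. What remains true is that none of these adjusts for period.
- **The change of mode was not clean.** Telephone was allowed from the outset for clients and was universal for caregivers. Period is therefore not the same as mode, and the mode argument does not reach caregiver outcomes.
- **Within-arm changes are descriptive.** Setting an assumed within-arm drift beside the planned between-arm difference compares unlike quantities. Nor is the province subgroup undermined by a common shift, which cancels in a group-by-province interaction.
- **The detail may sit in an analysis plan.** This carries less weight. The opening of Methods says all pandemic changes are described at the end of that section, and the statistical part there raises the telephone problem without giving an analysis for it.

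**Conclusion.** The point holds as a modest improvement to the analysis. The article identifies a period-linked change in data collection and possibly in case mix, and no stated model or sensitivity analysis adjusts for it.

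Under an arm-neutral shift the cost is precision only: about 0 to 5% in SE for 2 to 6 MCS points, just under 6% in the least favourable pattern, and at most 0.789 − 0.763 = 2.6 percentage points of power in the two-sample calculation at 5 points.

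A bias of up to about 0.2 points (0.27 at the extreme, or 0.27 / 3.68 = 7% of the planned effect) needs two further conditions: arm-differential loss in the interrupted cohort, and an imputation model without period. The article reports no such loss and does not specify the imputation model, so a claim of actual bias is not supported.

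The sizes rest on assumed shifts, cohort shares and correlation. The absence of a period term from the stated analyses does not.

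**What to change.** 1. Define a period cohort with three levels from the T1 date and the scheduled T2 date (T1 plus 6 months) relative to 16 March 2020: before/before, before/after, after/after. Using the scheduled date fixes it at enrolment and makes it identical in definition for both arms.
2. Include it in the imputation model and as a covariate in the client-outcome ANCOVA. If the primary model is to stay as stated, make it at least a named sensitivity analysis of the primary outcome.
3. Record the actual interview mode at T1 and T2, because the cohort captures period and telephone was possible before the stop.
4. Show the descriptive within-arm changes by cohort.
5. Reword the Recruitment paragraph of the COVID-19 modifications so that chronic-condition count is not offered as the handling of recruitment-period differences.

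Cost: two degrees of freedom and a change of wording. The dates follow from the interview schedule; mode may have to be retrieved for interviews already done. Adding the term to the primary model is a departure from the model now stated and should be documented as such. The sensitivity-analysis route avoids that.
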